#### Procedures

The Wisconsin Upper Respiratory Symptom Survey (**Attachment 1**) is an empirically derived patient-oriented illness specific quality-of-life evaluative outcomes instrument. It is a validated questionnaire in English and is now translated into Spanish, Japanese, French, German, Korean, Russian, and Ukrainian, with high correlation of previous questionnaires aimed to evaluate the presence of upper respiratory symptoms. It is also designed to reflect the impact of colds in quality of life and evaluate the severity through time [9, 37, 38]. This questionnaires correlate with laboratory assessed measures in a induced respiratory infections clinical trial[39]. This is a 21 items questionnaire, based on a 7 point Likert-type severity scale. To those will also be associated the items for headache, body-ache and fever [10, 40]. Questionnaire, WURSS-21 will be given to the included cases and controls, to be completed during 6 days and at the third

day it will be also filled in a validated questionnaire in Portuguese, MOS SF-36 (**Attachment 2**) [41, 42] of quality of life for convergent validity evaluation.

Demographic characteristics (age, gender, education, smoking habits, allergic diseases) will be collected when the questionnaire is delivered, written informed consent will be obtained if the patient decides to fill the questionnaire.

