#### Participants

All patients that require an unscheduled appointment due to acute illness in a primary health care center (USF Progresso, Perafita, Unidade Local de Saúde de Matosinhos) and from the Department of Allergy and Clinical Immunology from Centro Hospitalar de São João will be recruited. The inclusion criteria for respiratory infections cases are: over or equal 16 years of age, physician diagnosis of respiratory tract infections, with onset of symptoms within 48h and with Jackson score for respiratory infections over 3 or higher. In Jackson score eight symptoms (sneezing, nasal discharge, nasal obstruction, sore throat, cough, headache, malaise and chilliness) are classified as 0=absent, 1=mild, 2=moderate or 3=severe and presence of at least one of the first four cold specific symptoms is required for diagnosis. All those patients that attend to the primary care center or allergy department for other reason except respiratory symptoms/infections will be proposed to enroll the study project as controls. Exclusion criteria are: under 16 years of age, all patients with basal or throat symptoms that started more than 48h before they searched medical care. Results provided from patients with allergy and those without allergy complains will be compared for changes in respiratory symptoms score and in quality of life changes.

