#### Validation

Content validity of the Wisconsin questionnaire survey was previously studied in the validated versions of WURSS-44 and the short form WURSS-21[9, 38]. In the short form, will be assessed 7 different domains: global day severity, global change since yesterday, cough, throat, nasal, tiredness, functional/activity and other (head congestion). It will be also included

headache, body ache and fever to these domains, which has been used for WURSS-24 [10, 40].

Convergent validity will be assessed by comparison with a health related quality of life questionnaire, SF-36, already validated, which will be filled in at the third day of disease.

For criteria validity, the questionnaire will be compared between patients with respiratory infections and without respiratory infections diagnosed by physicians (which is the gold standard for respiratory infections diagnosis). Furthermore, inclusion criteria use the previously known Jackson criteria widely applied for respiratory infections diagnosis[8]. Both patients will fill WURSS during 6 days and SF-36 on the third day.

Reliability will be evaluated by the application of the same questionnaire through a 6 day period, first three days will be compared using internal consistency measures. As a respiratory infection symptom will change through time (patients will be asked if comparing to the previous day they feel that my cold is very much better, somewhat better, a little better, the same, a little worse, somewhat worse and very much worse) responsiveness to the questionnaire will be evaluated through already published methods[9, 44], namely Guyatt's responsiveness index. This index demands the calculation of Minimal important difference, the mean value of day-to-day changes. Also the mean squared error of the scores will also be needed, which is based on those subjects reporting the same state.

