#### 4.3.1. Cross-cultural translation and Validation of WURSS (I)

For statistical analysis of questionnaire validation factorial analysis will be used for content validity evaluation using the 7 identified domains of WURSS-21 plus headache, body-ache and fever, which are included in WURSS-24. This approach combines exploratory and confirmatory procedures, using weighted least square estimates employing diagonal weight matrix techniques to seek common factors between the domains; all questioned items will be included in the analysis. Convergent validity will be provided by Pearson correlations between WURSS-21 scores in the first day and SF-36 scores in the third, as this measures health state in the last 4 weeks. For criterion validity sensitivity, specificity and predictive positive values will be calculated, as well as area under the curve. For internal consistency Cronbach's alpha coefficient in each domain based on the average of scores from the first three days will be calculated and also comparison between the first and last day. To evaluate each day, responsiveness index will be calculated which is equal to minimal important differences (MID)/ $\sqrt{(2\text{mean squared error})}$ .

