##### Sample size calculation

Sample size was calculated assuming the worst proportion for an item, based in the previous published literature, which was chest congestion, that occurred in a prevalence of 75,7%, then assuming a confidence interval of 0,95% and a  $\alpha=0,05$  (with a standard normal deviate for a two-sided  $\alpha$ ), the required number would be 280 participants. This sample is adequate for the target factorial analysis in which 24 items will be used (WURSS-21 + headache, body ache and fever). For controls comparison and predictive validity evaluation, assuming that WURSS has a Sensitivity of 0,85 and Specificity of 0,44, and the fact that 70% of the population experiences a cold in a given year[9, 39], for a desired precision of 0,05 for the sensitivity and for a specificity of 0,1 the sample size population needed will be 281 participants. The largest population of 281 patients will be chosen as target for evaluation.

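### Study I collects WURSS-21 and SF-36 from cases and controls but does not limit the factor analysis, Cronbach's alpha or WURSS/SF-36 correlation to cases, and its factor-analysis sample counts controls

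*Protocol*

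**What the plan says.** In section 4.1.1 (Procedures), "WURSS-21 will be given to the included cases and controls, to be completed during 6 days". The same sentence adds SF-36 on the third day and gives its purpose: "of quality of life for convergent validity evaluation". The Validation text repeats this for both groups: "Both patients will fill WURSS during 6 days and SF-36 on the third day". Controls are patients who attend "for other reason except respiratory symptoms/infections will be proposed to enroll the study project as controls".

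Other text points to cases. In the Validation paragraph on convergent validity, SF-36 is the questionnaire "which will be filled in at the third day of disease", and section 4.2.2 also ties it to the third day of illness.

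Only criterion validity is described as a comparison of patients with and without infection. For the other statistics section 4.3.1 names no population:

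- "Convergent validity will be provided by Pearson correlations between WURSS-21 scores in the first day and SF-36 scores in the third";
- "For internal consistency Cronbach's alpha coefficient in each domain based on the average of scores from the first three days will be calculated";
- the factor analysis, said only to include all items.

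The sample size text derives 280 from the prevalence of one symptom and says of it: "This sample is adequate for the target factorial analysis in which 24 items will be used". It then derives 281 from sensitivity and specificity, with 70% of the population having a cold, and takes 281 as the target.

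**The concern.** The validation should show that the Portuguese items hang together, and track quality of life, among people who have a respiratory infection. Cases enter on a physician diagnosis plus a Jackson score threshold. Five of the eight Jackson symptoms (sneezing, nasal discharge, nasal obstruction, sore throat, cough) recur among the WURSS symptom items in section 4.2.1, and headache is one of the three added items. If people selected on these symptoms are pooled with people attending for another reason, every item separates the groups, and the items correlate with one another through group membership even if they are unrelated among the sick.

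At stake is whether a high alpha or a dominant factor says anything about the translation. Study II relies on the instrument for its severity scores.

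**Working it through.** **1. The plan's own sample sizes.** The formula is n = z²p(1−p)/d², with z = 1.96.

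- Item prevalence, p = 0.757. The half-width d = 0.05 is my assumption, because the printed precision is unclear: 3.8416 × 0.757 × 0.243 / 0.0025 = 283, against the stated 280.
- Sensitivity 0.85, d = 0.05: 3.8416 × 0.85 × 0.15 / 0.0025 = 196 cases; 196 / 0.70 = 280, against the stated 281.
- Specificity 0.44, d = 0.10: 3.8416 × 0.44 × 0.56 / 0.01 = 94.7 controls; 94.7 / 0.30 = 316. This does not give 281, so the target appears to come from sensitivity.

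The target of 281 is therefore a total of cases and controls.

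**2. Cases within 281.**

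- At 70%: 0.70 × 281 = 197 cases and 84 controls. For 24 items, 197/24 = 8.2 per item; pooling gives 281/24 = 11.7.
- Item-prevalence half-width with 197 cases: 1.96 × √(0.757 × 0.243 / 197) = 0.060. Keeping 0.05 needs 283 cases, or 283/0.70 = 404 participants.
- The recruitment split is not fixed in the protocol. At an assumed 50:50 there are about 140 cases, 5.9 per item, half-width 0.071.

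**3. Alpha under pooling.** The protocol gives no group means or SDs, so these inputs are assumptions. Let π = 0.70 be the case share, so π(1−π) = 0.21. For items independent within group, pooled inter-item r = between-group variance / total variance, and standardized alpha = kr / (1 + (k−1)r). Take cases at mean 3, SD 1.7 on the 0–7 scale.

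- Controls at 0: between = 0.21 × 9 = 1.89; within = 0.7 × 2.89 = 2.023; r = 1.89/3.913 = 0.483. Three-item alpha = 1.449/1.966 = 0.74.
- Controls mildly symptomatic (mean 1, SD 1.2): between = 0.21 × 4 = 0.84; within = 2.023 + 0.3 × 1.44 = 2.455; r = 0.84/3.295 = 0.255. Three-item alpha = 0.765/1.51 = 0.51.

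The case-only alpha is 0 in both settings. If the items do cohere (within-group r = 0.4, three-item alpha 0.67), a separation of d = 1 to 3 within-group SDs raises pooled alpha to 0.75–0.92, using pooled r = (r + 0.21d²)/(1 + 0.21d²).

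**4. Factor structure.** Take three uncorrelated 8-item factors with within-factor item correlation 0.49. Each has eigenvalue 1 + 7 × 0.49 = 4.43, or 18% of 24. After pooling, the first eigenvalue is (4.43 + 24 × 0.21d²)/(1 + 0.21d²).

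| d (SD) | First eigenvalue | Share of 24 |
|---|---|---|
| 1 | 7.83 | 33% |
| 2 | 13.36 | 56% |
| 3 | 17.23 | 72% |

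The dominant factor is case status.

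**5. WURSS/SF-36 correlation.** Let ρ be the within-group correlation, and let cases be dW SDs higher on WURSS and dS SDs worse on SF-36. Pooled r = (ρ − 0.21·dW·dS) / √[(1 + 0.21dW²)(1 + 0.21dS²)].

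- ρ = 0, dW = 1–3, dS = 0.3–0.5: r = −0.06 to −0.18. At dS = 1.5 it reaches −0.46 (dW = 3).
- ρ = −0.3, dW = 1–3, dS = 0.3–0.5: r = −0.28 to −0.37, so little changes.
- ρ = −0.3, controls 0.3 SD worse on SF-36 (dS = −0.3), dW = 2: (−0.3 + 0.126)/√(1.84 × 1.0189) = −0.13, a true association weakened.

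**The case against.** Pooling is never stated. Controls need WURSS for criterion validity, so handing them the form does not fix a pooled analysis, and the population for each psychometric statistic could be left to a statistical analysis plan. The Summary says that participants with respiratory infections will be selected for the validation, section 3 sets the aim in patients with such infections, and the 75.7% symptom prevalence behind the 280 fits only ill people. All of this leans towards cases.

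It shows that the intention may have been cases only. It does not make the text say so. Section 4.1.1 collects SF-36 from both groups expressly for convergent validity, which criterion validity does not require, and the target is a mixed total. The document contradicts itself, which is more than detail left for later.

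Four stronger readings are tempting and not supported:

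- *Controls are symptom-free.* The protocol only says that respiratory symptoms are not why they attend. They may be acutely ill or allergy-clinic patients, and may score on tiredness, sleep, activity, headache or fever. Hence the range in step 3.
- *The statistics mainly re-detect who was recruited as a case.* That depends on the group gaps. It is plausible for alpha and factor structure when the groups are well separated, but not established for SF-36, where a modest gap creates only a small correlation and the opposite gap masks a real one.
- *Pooling inflates the responsiveness index by a known factor.* Controls with little change would shrink the same-state error but also dilute the mean day-to-day change in the numerator, and the transition question asks about the respondent's cold. No inflation figure follows.
- *Study II's infection outcome is compromised.* Section 4.2.1 defines an episode by a yes/no cold question, a cold symptom and a Jackson score. WURSS supplies severity scores.

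**Conclusion.** The concern holds as an unresolved conflict in the protocol with a predictable bias if the analyses are run on all returned forms. For alpha and factor structure the direction is clear: upward, and towards one general factor. Three items unrelated within group would show a pooled alpha of about 0.5 to 0.75, and a first factor could grow from 18% to between 33% and 72% of the variance. These sizes rest on a 70% case share and assumed group separations; the protocol supplies no separations, and its 70% is a yearly cold proportion, not a recruitment quota. For the SF-36 correlation neither the direction nor a definite size can be claimed.

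The sample-size point rests on the protocol's own figures. The 280 called adequate for the factor analysis would have to be cases, while the 281 target holds about 197. This should be corrected; it does not invalidate the study.

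**What to change.** - In section 4.3.1, state that the factor analysis, Cronbach's alpha, the WURSS/SF-36 correlations and the responsiveness index are computed in respiratory-infection cases only, or reported within group. Use controls for criterion validity (sensitivity, specificity, predictive value, area under the curve).
- Reconcile the Procedures and Validation text of section 4.1.1 with section 4.2.2 on who completes SF-36, when, and for what purpose.
- In the sample size text, give the number of cases for the factor analysis (about 197 at the 70% share, roughly 8 per item) and the item-prevalence precision this allows (about ±0.06).

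The cost is a change of wording, a smaller sample for these statistics (about 197 instead of 281), and probably lower reported coefficients. If a half-width of 0.05 for item prevalence is to be kept, the cost is larger: about 404 participants at 70% cases.

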#### Cross-cultural translation

Cross-cultural translation will be provided by investigators that contact daily with patients with respiratory infections and follow their course. This procedure will be based in the previous published guidelines by Baiardini et al.[43] and all items will be included in the cross cultural translation process (namely questionnaire instructions, items and response choices). The linguistic validation will consist on three steps:

1. Forward translation (translate from source language, English, to target language, Portuguese) by two translators, native speakers in the target language and bilingual in the source language, supported by an experienced specialist in respiratory infection treatment and diagnosis; translators will independently produce a forward translation of the questionnaire, then a combined version, obtained by the agreement on a single reconciled version with all elements (translators and physician)
2. Backward translation (translation of the first reconciled forward version of the questionnaire back into the source language): requires a translator with no previous access to the questionnaire, native speaker of the source language and bilingual in the target language, this version will be sent to the authors for review and comment; then a comparison will be made with the original source version to detect any misunderstandings, mis-translations or inaccuracies in the forward version of the questionnaire
3. Patient testing (comprehension test): the final consensus version will be administered to a sample of 10 respondents, native speakers of the target language, over 16 years old, in a face to face interview, during which participants will be inquired if any difficulties were found in understanding the questionnaire and check the interpretation of all items; if any problem is encountered the interviewer should ask the person to propose alternatives and test alternative translations. This is aimed to determine whether the translation is acceptable, understood and if the language is simple/ appropriate. During interview, data will be collected: number of interviewed, age, difficulties and solutions.

From this report a third and final version will be produced

#### Validation

Content validity of the Wisconsin questionnaire survey was previously studied in the validated versions of WURSS-44 and the short form WURSS-21[9, 38]. In the short form, will be assessed 7 different domains: global day severity, global change since yesterday, cough, throat, nasal, tiredness, functional/activity and other (head congestion). It will be also included

headache, body ache and fever to these domains, which has been used for WURSS-24 [10, 40].

Convergent validity will be assessed by comparison with a health related quality of life questionnaire, SF-36, already validated, which will be filled in at the third day of disease.

For criteria validity, the questionnaire will be compared between patients with respiratory infections and without respiratory infections diagnosed by physicians (which is the gold standard for respiratory infections diagnosis). Furthermore, inclusion criteria use the previously known Jackson criteria widely applied for respiratory infections diagnosis[8]. Both patients will fill WURSS during 6 days and SF-36 on the third day.

Reliability will be evaluated by the application of the same questionnaire through a 6 day period, first three days will be compared using internal consistency measures. As a respiratory infection symptom will change through time (patients will be asked if comparing to the previous day they feel that my cold is very much better, somewhat better, a little better, the same, a little worse, somewhat worse and very much worse) responsiveness to the questionnaire will be evaluated through already published methods[9, 44], namely Guyatt's responsiveness index. This index demands the calculation of Minimal important difference, the mean value of day-to-day changes. Also the mean squared error of the scores will also be needed, which is based on those subjects reporting the same state.

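### Study I defines the minimal important difference as an unrestricted mean of day-to-day changes, so the responsiveness index depends on how fast the sample recovers

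*Protocol*

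**What the plan says.** Protocol section 4.1.1 (Validation) states that "responsiveness to the questionnaire will be evaluated through already published methods[9, 44], namely Guyatt's responsiveness index". The same sentence introduces the daily rating of change, with the levels "very much better, somewhat better, a little better, the same, a little worse, somewhat worse and very much worse". Two rules for the index follow:

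- Numerator: "This index demands the calculation of Minimal important difference, the mean value of day-to-day changes". No rating level, sign convention or population is attached.
- Denominator: a mean squared error, "which is based on those subjects reporting the same state".

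Section 4.3.1 gives the formula as the MID divided by the square root of twice the mean squared error: "To evaluate each day, responsiveness index will be calculated which is equal to minimal important differences". It does not redefine the MID.

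On who supplies the scores, section 4.1.1 (Procedures) says that "WURSS-21 will be given to the included cases and controls, to be completed during 6 days". Section 4.2.1 leaves the first and last items out of the daily summary score and analyses them separately.

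**The concern.** A minimal important difference is the score change that goes with the smallest change patients notice. An unrestricted mean of day-to-day changes is something else: it is the average speed and direction of the illness in the people who returned the diary. Two samples could complete an identical questionnaire, equally sensitive to a small change, and yield different indices because one recovered faster.

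The design allows the mix of ratings to vary. Cases enter within 48 hours of symptom onset and are followed for six days, so some person-days may be worsening and others recovery. Controls have no respiratory infection and would be expected to show little change, which would pull an unrestricted mean towards zero.

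At stake are the responsiveness index and the MID reported for the Portuguese version. Section 10 presents the instrument as one for monitoring infections in clinical and experimental settings, and these are properties that such monitoring relies on.

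**Working it through.** **The text.** The two sentences on the index stand side by side in section 4.1.1. The denominator is restricted by the patient's own rating and the numerator is not. With the restriction applied to one term only, the natural reading is that the other is unrestricted. Nothing in section 4.3.1 or elsewhere changes that.

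**Figures to reproduce.** There are none. The protocol states no MID, mean squared error (MSE) or index value.

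**Illustration.** The formula is the protocol's (section 4.3.1): index = MID / √(2 × MSE). All other inputs are assumptions:

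- mean score change of +3, +2, +1, 0, -1, -2, -3 units from *very much better* to *very much worse*, with improvement positive;
- MSE = 1, so √(2 × MSE) = 1.414;
- four hypothetical mixes of the seven ratings, in the same order.

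Worked example for the recovering mix (15/25/25/20/8/5/2%):

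- improvement: 0.15×3 + 0.25×2 + 0.25×1 = 1.20
- worsening: 0.08×1 + 0.05×2 + 0.02×3 = 0.24
- signed mean: 1.20 - 0.24 = 0.96; index 0.96/1.414 = 0.68
- absolute mean: 1.20 + 0.24 = 1.44; index 1.44/1.414 = 1.02

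| Mix of ratings (%) | Signed mean | Index, signed | Absolute mean | Index, absolute | Index, *a little better* only |
|---|---|---|---|---|---|
| Recovering (15/25/25/20/8/5/2) | 0.96 | 0.68 | 1.44 | 1.02 | 0.71 |
| Fast recovery (35/30/15/12/4/3/1) | 1.67 | 1.18 | 1.93 | 1.37 | 0.71 |
| Balanced (5/12/20/26/20/12/5) | 0.00 | 0.00 | 1.18 | 0.83 | 0.71 |
| Worsening (3/7/15/25/25/17/8) | -0.45 | -0.32 | 1.21 | 0.86 | 0.71 |

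The last column is 1/1.414 = 0.71 in every row, because the mean within one rating level does not depend on how many patients chose the other levels.

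The absolute column uses the absolute value of each level's mean. Averaging individual absolute changes would come out at least as high, because random day-to-day variation would add to the mean even among patients who report no change.

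**The anchor.** The rating needed to restrict the numerator is already collected daily. Section 4.2.1 keeps the first and last items out of the summary score, so the comparison-with-yesterday item can serve as an anchor outside the score.

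**The case against.** The strongest defence is that the MID sentence is shorthand. It follows directly on the rating scale, the named index and two cited validation papers, and those papers may restrict the MID to a rating level. They cannot be consulted here, so this cannot be excluded. If they do restrict it, the protocol's sentence misdescribes its own method and still needs correcting. A statistical analysis plan could also settle which person-days enter, but the protocol does not leave the numerator open: it states a rule.

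Other parts of the defence limit what may be claimed:

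- The protocol does not say that *all* changes are averaged. That is an inference from the missing restriction.
- A reader might infer that a responsive questionnaire will look unresponsive, or that the index will take the wrong sign early in the illness and be too high late. The documents do not support that. It would need signed changes, and the text does not choose between signed and absolute. It would also need an MID re-estimated each day, whereas section 4.3.1 asks only for the index by day and a single MID pooled over six days fits the wording equally well. A wrong sign further requires worsening to outweigh improvement.
- The illustration contains no score, error or rating frequency from the protocol. It shows that the index depends on the mix; it does not predict a value.

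**Conclusion.** The point holds in limited form. The numerator rule, applied as written, does not give a minimal important difference, because it carries no restriction to a small perceived change and does not exclude controls. If changes are signed, improvement and worsening partly cancel. If they are absolute, there is no cancellation, but in the illustration the index is overstated, at 0.83 to 1.37 against 0.71, or about 1.2 to 1.9 times. Both results rest wholly on the assumed changes, error and rating mixes. The direction and size of the error in the real data cannot be known from the protocol.

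The effect is confined to the responsiveness result of study I. The target of 281 participants does not use the MID, study II relies on summed WURSS scores and regression, and the randomized studies IV and V are untouched. The correction should be made because the stated rule gives the wrong quantity and the data for the right one are already collected.

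**What to change.** In section 4.1.1 (Validation), with matching text in section 4.3.1, define the MID as the signed mean change in daily score between consecutive days, improvement counted as positive, among **cases** who rate themselves *a little better*. Either reverse the sign for *a little worse* and pool, or report that level separately. Do not average individual absolute changes: that would count score movements opposite to the rating as improvement and inflate the MID with noise. Keep the mean squared error from cases who rate themselves *the same*.

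The cost is one sentence in each section and no new data. Fewer person-days will feed each estimate. If daily numbers are small, pool the MID over the six days.
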